### Data analysis

As the trial is a pragmatic parallel group RCT data will be reported and presented according to the revised CONSORT statement and statistical analyses will be performed on an intention-to-treat basis. All statistical exploratory tests will be two-tailed with α = 0.05. Baseline demographic and health-related quality of life data (SF-36) will be assessed for comparability between the treatment groups. The primary aim is to compare the effect of loaded exercise versus usual physiotherapy. The mean SPADI total score at 12 weeks follow-up is the primary efficacy response variable. A two independent samples t-test will be used to compare mean SPADI total scores between the groups (loaded exercise and usual physiotherapy groups). In the event of differences between the groups with respect to baseline measurements, multiple regression or analysis of covariance (ANCOVA) will be used to adjust the treatment effect for these variables. Secondary outcomes will be analysed in a similar way. For the repeated PSFS assessments at baseline and termination of treatment and (SPADI, SF-36) assessments at baseline, 12, 24 and 52 weeks a summary measure such as the Area Under the Curve (AUC) will be calculated for each patient. A two independent samples t-test will be used to compare mean AUC between the groups (loaded exercise and usual physiotherapy groups).

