**Methods/Design:**

A single-centre pragmatic unblinded parallel group randomised controlled trial will evaluate the effectiveness of a self-managed loaded exercise programme versus usual clinic based physiotherapy. A total of 210 study participants with a primary complaint of shoulder pain suggestive of a rotator cuff disorder will be recruited from NHS physiotherapy waiting lists and allocated to receive a programme of self-managed exercise or usual physiotherapy using a process of block randomisation with sealed opaque envelopes. Baseline assessment for shoulder pain, function and quality of life will be undertaken with the Shoulder Pain & Disability Index, the Patient Specific Functional Scale and the SF-36. Follow-up evaluations will be completed at 3, 6 and 12 months by postal questionnaire. Both interventions will be delivered by NHS Physiotherapist’s.

An economic analysis will be conducted from an NHS and Personal Social Services perspective to evaluate cost-effectiveness and a qualitative investigation will be undertaken to develop greater understanding of the experience of undertaking or prescribing exercise as a self-managed therapy.

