### Baseline/outcome assessment

After the participants have been assessed for eligibility and consent has been gained, prior to randomisation, they will complete a range of appropriate patient-reported outcome measures to establish baseline pain, function, quality of life and level of self-efficacy. Additionally, the participants’ preference for one treatment or the other, if they had a free choice, will be noted to enable analysis of the effect of preference on outcome.

The primary aim of the proposed study is to evaluate the clinical and cost-effectiveness of self-managed loaded exercise versus usual physiotherapy for rotator cuff disorders. The primary outcome measure will be the Shoulder Pain & Disability Index (SPADI) [24] score at 12 weeks. SPADI is a self-report measure specifically developed to evaluate pain and function in patients with shoulder pathology [25]. It is a commonly used measure which has been validated for use in this patient population and a minimally clinically important change of 10 points has been identified [25]. The SPADI includes 13 items divided into 2 sub-scales; pain (5 items), disability (8 items). The responses are indicated on a visual analogue scale where 0 = no pain/no difficulty and 10 = worst imaginable pain/so difficult it requires help. The items are summed and converted to a total score out of 100.

The Short-form 36 (SF-36) is a generic measure of health related quality of life [26] and is the most widely used measure of this nature. The SPADI & SF-36 will be repeated at 12, 24 and 52 weeks and returned by post. These measures will be complemented by the patient specific functional scale (PSFS) which is a patient-specific outcome measure which investigates functional status and is intended to complement the findings of generic or condition-specific measures [27]. The PSFS has been shown to be valid and responsive in various musculoskeletal populations [28]. Due to the nature of the PSFS, this measure will be completed at baseline and then completed, until the end of the treatment episode, in the presence of the attending physiotherapist. Treatment duration is likely to be in the region of 3 months with the PSFS being completed at 1, 2 and 3 months post baseline.

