### Sample size calculation

The sample size calculation is based upon the primary outcome measure, the SPADI, where a 10-point change is regarded as a minimally clinically important change in shoulder function [24]. Assuming a standard deviation of 24 points, a power of 80% and a (two-sided) significance level of 5%, 91 participants per group will be required. We will allow for a 15% loss to follow-up and aim to recruit 105 participants per group. Data from the Physiotherapy department at Doncaster & Bassetlaw Hospitals NHS Foundation Trust indicates that 70 potentially suitable patients are referred for treatment each month. Hence a recruitment rate of 17 to 18 per month is felt to be realistic and manageable in the allotted timescale.

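### Adjustment of the primary SPADI comparison depends on observed baseline differences; ANCOVA on baseline SPADI should be fixed in advance

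*Protocol article*

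**What the plan says.** The Data analysis section sets the endpoint: "The mean SPADI total score at 12 weeks follow-up is the primary efficacy response variable". It sets the test: "A two independent samples t-test will be used to compare mean SPADI total scores between the groups". It then makes adjustment conditional: "In the event of differences between the groups with respect to baseline measurements, multiple regression or analysis of covariance (ANCOVA) will be used", the purpose being "to adjust the treatment effect for these variables". The variables adjusted for are thus the ones found to differ. The section does not say whether the adjusted result replaces the t-test or stands beside it. Secondary outcomes are to be handled in a similar way.

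The same section announces a baseline check: "Baseline demographic and health-related quality of life data (SF-36) will be assessed for comparability between the treatment groups". Baseline SPADI is not named in that sentence, although the trigger sentence speaks of baseline measurements in general.

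Baseline SPADI is available. The abstract says: "Baseline assessment for shoulder pain, function and quality of life will be undertaken with the Shoulder Pain & Disability Index", and the Baseline/outcome assessment section places the baseline measures before randomisation. The same instrument is then used at follow-up: "The SPADI & SF-36 will be repeated at 12, 24 and 52 weeks and returned by post".

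**The concern.** Allocation is random, so any baseline difference between the arms is a chance event. Whether a covariate happens to differ says little about whether it should be in the model. What matters is how well it predicts the outcome. Under the stated rule, a strongly prognostic baseline score that looks balanced is left out, while a variable of no prognostic value that happens to differ is put in.

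Two things are at stake. First, the form of the analysis of the primary endpoint, and the covariates in it, are settled only after baseline data have been examined, and two candidate results can exist with no statement of which one counts. Second, baseline SPADI is the same scale as the endpoint and is collected from participants anyway, yet the default primary comparison makes no use of it. The precision it could supply is given up.

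**Working it through.** **Inputs from the Sample size calculation section.** Difference 10 points ("a 10-point change is regarded as a minimally clinically important change in shoulder function"), SD 24, two-sided 5% level, 80% power, 91 per group required, 15% loss allowed for, 105 per group recruited.

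**Assumed inputs.** The correlation r between baseline and 12-week SPADI is not given; I take 0.3, 0.5 and 0.6. The article gives no threshold for a baseline difference, so I take the trigger as p<0.05 or p<0.10 on baseline SPADI.

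**1. The plan's own figure.** n per group = 2 × (1.960 + 0.842)² × 24² / 10² = 90.4, rounded up to 91. It reproduces.

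**2. Number analysed.** 105 × 0.85 = 89.25, so 89 per arm.

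**3. Unadjusted t-test.** Standardised difference 10/24 = 0.417; noncentral t with 89 per arm gives power 78.9%. The small shortfall from 80% comes from the loss allowance (91 × 1.15 = 104.65, whereas 91/0.85 = 107.1), not from the choice of test.

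**4. ANCOVA in all cases.** The residual SD becomes 24 × √(1 − r²), and the power calculation is repeated with it.

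| r | residual SD | ANCOVA power, 89 per arm | n per group for 80% power |
|---|---|---|---|
| 0.3 | 22.89 | 82.6% | 83 |
| 0.5 | 20.78 | 89.1% | 68 |
| 0.6 | 19.20 | 93.3% | 58 |

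**5. The conditional rule.** I simulated bivariate normal baseline and outcome, 89 per arm, 100,000 trials per setting: ANCOVA if the trigger fires, t-test otherwise. Each cell gives trigger p<0.05, then p<0.10.

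| r | power of the rule | type I error of the rule |
|---|---|---|
| 0.3 | 79.4%, 79.5% | 4.7%, 4.5% |
| 0.5 | 80.2%, 81.1% | 4.3%, 4.1% |
| 0.6 | 80.5%, 81.6% | 4.0%, 3.6% |

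The rule recovers little of the gain because it uses ANCOVA in only about 5% or 10% of trials. Its error falls below 5% because the t-test is kept for the balanced samples, where its standard error is too large, and dropped for the imbalanced ones, where most of its false positives occur.

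**6. Misuse of the rule.** If both analyses were always run and the smaller p-value reported, type I error would be 6.3% to 7.8% over these correlations. If the smaller p-value were taken only when the trigger fires, it would be 5.1% to 5.3%.

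**The case against.** The strongest defence is that the planned test is sound. A two-sample t-test on 12-week SPADI is valid under randomisation, it is the basis on which 91 per group was derived, and the trial is not underpowered because of it. What is lost is a possible gain, and its size rests wholly on a correlation that the article does not give; at r = 0.3 it is only about 4 points. All of that stands.

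The text can also be read as an unconditional primary t-test with a supportive adjusted analysis. On that reading the primary p-value does not depend on the baseline data. The wording allows this but does not say it, and that ambiguity is part of the point.

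A reader might infer that the rule inflates the false-positive rate. The documents do not support this. Applied as written, the rule is conservative (step 5). An error of 6 to 8% needs the trigger to be ignored and the better result to be picked, and the plan proposes neither.

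A reader might also infer that baseline SPADI is wasted. That is too strong. It enters the planned area-under-the-curve summary, and it counts as a baseline measurement that could enter the adjustment if judged imbalanced.

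Finally, a threshold, a covariate list and the choice between regression and ANCOVA could properly be left to an analysis plan, and their absence from an article is not the criticism. The conditional rule is stated outright, and that rule is the criticism.

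Adjusting when imbalance is seen does have a rationale, since a chance imbalance in a prognostic score distorts the unadjusted comparison in that trial. ANCOVA fixed in advance gives the same protection without the trigger.

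**Conclusion.** The point holds as one of data-dependent analysis and forgone precision. At 89 per arm, ANCOVA in all cases would raise power from 79% to about 83%, 89% or 93% at r of 0.3, 0.5 or 0.6, while the conditional rule stays at 79 to 82%, with type I error of about 3.5 to 4.7%. These figures rest on the article's difference of 10 and SD of 24, approximately normal scores, the assumed correlations, and a trigger based on baseline SPADI alone. A trigger that looked at other variables as well would fire more often: with ten independent variables each tested at 5%, the chance of at least one is 1 − 0.95¹⁰ = 40%. Adjustment would then often be for variables chosen by chance.

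It does not follow that the trial is invalid, underpowered by its test, or prone to excess false positives. The grade is should-fix: a free improvement to the analysis of the primary endpoint.

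**What to change.** In the Data analysis section, or in the statistical analysis plan before outcome data are seen:

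- State that the primary analysis is ANCOVA of 12-week SPADI total score on treatment group and baseline SPADI, whatever imbalance is seen.
- Delete the condition that ties adjustment to observed baseline differences. Keep the baseline comparison as description only.
- Analyse each secondary outcome in the same way, with its own baseline as covariate (SF-36, PSFS).
- Keep the unadjusted t-test on 12-week SPADI as a sensitivity analysis, labelled as such.

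The cost is about one sentence of text. No new data and no more participants are needed, and the sample size of 105 per group can stay as it is.

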### The intervention

The intervention is self-managed loaded (against gravity or resistance) exercise. The exercise, prescribed by the physiotherapist but completed by the patient independently, involves exercising the affected shoulder against gravity, a resistive therapeutic band or hand weight over 3 sets of 10 to 15 repetitions completed twice per day. This exercise can be uncomfortable for the patient but is prescribed to ensure that the discomfort is manageable. Exercise prescription is guided by symptomatic response requiring that pain is produced during exercise that remains no worse upon cessation of that exercise [7,23]. Hence participants with more severe symptoms tend to commence a lighter regime to begin with. A typical programme is presented in Box 1.

**Box 1 T1:** Typical loaded exercise progression

1. Week 0: Baseline assessment:
·Resisted isometric (no movement) shoulder abduction (taking the arm out to the side) against a wall, or
·Resisted shoulder abduction from 0 to 30° using moderate resistance from Theraband (resistive band used for training purposes).
2. Week 3: Initial follow-up:
·Resisted shoulder abduction from 80 to 120° using light weight, e.g. tin of food.
3. Week 6: Second follow-up:
·Resisted shoulder abduction from 80 to 120° with progressively increasing repetition and weight, e.g. heavy Theraband or dumbbell.
4. Week 12: Final follow-up/discharge.

To maintain the pragmatic value of the study, in both arms of the trial, the treating physiotherapists will determine the number of sessions, frequency and point of treatment cessation. However, the emphasis of the intervention arm is towards self-management with supervision and guidance only offered by the physiotherapist [7,23].

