### Randomisation

Block randomisation will be carried out by an administrator based in the physiotherapy department but independent to the study. Following receipt of written informed consent and baseline assessment, a computer generated random number sequence indicating group allocation will be concealed in sealed opaque envelopes which will be consecutively numbered. The group allocation and baseline PSFS assessment will be attached to the patient referral for the attention of the treating physiotherapist in readiness for the programme of treatment.

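### The PSFS is summarised by an AUC that ends when treatment ends, with no stated standardisation for time, so any difference in treatment length between arms enters the comparison

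*Protocol article*

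**What the plan says.** The Data analysis section of the protocol article treats the longitudinal outcomes together. SPADI and SF-36 have fixed times: baseline, 12, 24 and 52 weeks. The PSFS does not: "For the repeated PSFS assessments at baseline and termination of treatment". For all of them, "a summary measure such as the Area Under the Curve (AUC) will be calculated for each patient", and then "A two independent samples t-test will be used to compare mean AUC between the groups". Nothing is said about dividing by the length of follow-up.

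The end of the PSFS window is a clinical decision. Under The intervention, in both arms, "the treating physiotherapists will determine the number of sessions, frequency and point of treatment cessation". The same paragraph adds that "the emphasis of the intervention arm is towards self-management with supervision and guidance only offered by the physiotherapist". The therapist knows the arm, because under Randomisation "The group allocation and baseline PSFS assessment will be attached to the patient referral for the attention of the treating physiotherapist".

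Baseline/outcome assessment describes a different series, "with the PSFS being completed at 1, 2 and 3 months post baseline", and limits collection: "this measure will be completed at baseline and then completed, until the end of the treatment episode, in the presence of the attending physiotherapist".

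**The concern.** An AUC compares patients fairly only if all are followed over the same window, or if it is divided by the window. Here the window closes at a date chosen after randomisation by someone who knows the allocation. If higher PSFS scores are better, a patient who recovers fast and is discharged early collects a smaller area than one who improves little over a longer course. A between-arm difference in treatment length would then appear as a difference in function, or hide or reverse a real one. This would happen even with complete and accurate PSFS data.

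Separately, two sections of the protocol name different PSFS assessment times, so the reader cannot tell which scores enter the analysis.

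**Working it through.** **The plan's own figures.** None is given for the PSFS. The only design calculation is for the SPADI, and it reproduces: 2 × (1.96 + 0.84)² × 24² / 10² = 90.4, so 91 per group. Recruiting 105 per group with 15% loss leaves 105 × 0.85 ≈ 89 per arm, which is used below.

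**Formula.** With two assessments P0 and P1 and treatment length T, the trapezoid AUC is T × (P0 + P1)/2. T multiplies the score whatever the scale.

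**Single-patient examples** (assuming 0-10, higher better):
- 3 to 8 over 6 weeks: 6 × 11/2 = 33 point-weeks. 3 to 5 over 12 weeks: 12 × 8/2 = 48. The better recovery scores lower.
- 4 to 7 over 12 weeks: 66. The same change over 9 weeks: 49.5.
- 4 to 8 over 11 weeks: 66, a tie with 4 to 7 over 12 weeks. Over 10 weeks it is 60, and the order reverses.

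**Group level.** Assumed, not in the documents: baseline mean 4 (SD 1.8), final mean 7 (SD 2.2), correlation 0.4, T with SD 3 weeks and independent of the scores, 89 per arm. Let M = (P0 + P1)/2. Its mean is 5.5 and its variance is (3.24 + 4.84 + 2 × 0.4 × 1.8 × 2.2)/4 = 2.81. The variance of the AUC is E(T)²·Var(M) + E(M)²·Var(T) + Var(M)·Var(T).

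For 10 v 12 weeks with identical function:
- Mean difference: 2 × 5.5 = 11 point-weeks.
- Variances: 100 × 2.81 + 30.25 × 9 + 25.3 ≈ 579 and 144 × 2.81 + 30.25 × 9 + 25.3 ≈ 702. The average is about 641, SD 25.3.
- SE: 25.3 × √(2/89) = 3.79, so z = 2.90 and the rejection rate is about 83%.

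Simulation (4,000 trials, scores held to 0-10) agrees:

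| Mean length (weeks) | True final difference | Raw AUC significant | Final score significant |
|---|---|---|---|
| 12 v 12 | 0 | 5% | 5% |
| 11 v 12 | 0 | about 30% | about 5% |
| 10 v 12 | 0 | 84% | about 5% |
| 9 v 12 | 0 | over 99% | about 5% |
| 12 v 12 | 1 point | about 26%, right direction | about 83% |
| 10 v 12 | 1 point, shorter arm better | about 41-43%, wrong direction | about 83% |

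With other assumed SDs (baseline 2, residual 2, 91 per arm, no bounds on scores) the rates for identical function are 29%, 80% and 99% at 11, 10 and 9 v 12 weeks. Wrong-direction significance at 10 v 12 is 31%.

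**Variants.** Under that second set of inputs, dividing each AUC by the patient's own T restores about 4-5% false positives at every gap. Its power for a 1-point benefit is only about 45-48%, because half of the summary is the baseline score. Subtracting the baseline without dividing by T does not help: 11%, 32% and 62% false positives at the same gaps.

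**The case against.** A reader might infer that the allocated arm does change treatment length. The documents do not say so. Discretion applies in both arms, and the self-management wording describes the style of care, not its duration. Box 1 shows discharge at week 12 in a typical intervention programme, and Baseline/outcome assessment expects about 3 months without separating the arms. With equal mean lengths the raw AUC keeps its 5% error rate. This stands, so the bias is conditional.

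The AUC is offered only as an example of a summary measure, and an analysis plan not shown could standardise it for time. This stands in part: the following sentence commits to comparing mean AUC, over a window the protocol itself ties to the end of treatment.

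It is tempting to say that the monthly PSFS scores go unused. That is not established. The Data analysis section says that secondary outcomes get a similar analysis to the primary, which may already mean a direct comparison of PSFS scores. It names no PSFS time point, however, and does not withdraw the AUC test.

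Finally, every PSFS input above is assumed, including the direction of the scale. If lower were better, the bias would reverse but would not vanish.

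**Conclusion.** The point holds in conditional form. As written, the PSFS summary mixes treatment length with function, and nothing in the protocol keeps length equal between arms. If mean lengths differ by one or two weeks, a nominal 5% test would reject in roughly 30% or 80-84% of trials with identical function. At a two-week gap it could significantly favour the worse arm in about 31-43%. These figures apply only to a raw AUC under the stated assumptions; they show what could happen, not what this trial will show. The loss of power needs no imbalance: about 26% against 83% for the final score when lengths are equal.

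The mismatch between monthly assessments in one section and baseline plus termination in the other is plain on the page and must be reconciled.

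The damage is confined to one secondary outcome. The 12-week SPADI comparison is unaffected, and SPADI and SF-36 have fixed assessment times.

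**What to change.** In Data analysis, drop the raw AUC for the PSFS. Compare PSFS scores adjusted for baseline PSFS, using a repeated-measures model on the 1, 2 and 3 month scores with the 3-month contrast as the target. Report treatment length by arm as a separate process measure. If any AUC is kept, state that it is divided by each patient's own follow-up time. Make Baseline/outcome assessment and Data analysis name the same PSFS times.

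The edit is a few sentences and needs no extra patients, but it has a cost. The PSFS is collected only until the treatment episode ends, so patients discharged before 3 months have no later scores. The model then relies on a missing-at-random assumption, with missingness created by the same discharge decision. Add a sensitivity analysis that uses the last score at the end of treatment. The 83% power above belongs to that end-of-treatment score, not to the repeated-measures model, whose power was not calculated. A fixed-time comparison free of this assumption would need the PSFS to be collected after discharge.

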As with the clinical outcomes, economic analysis will be on an intention-to-treat basis. The between groups differences will be compared using 2-independent samples t-tests. The QALY value will be estimated using straight line interpolation between data points. So, for example, if a patient reports quality of life (QoL) equal to 1 at each time point during the trial this will equate to a QALY of 1 and if they report QoL equal to 0.5 at each time point during the trial this will equate to a QALY of 0.5. Mean incremental costs and QALYs will be combined into an incremental cost effectiveness ratio (ICER) to enable assessment of the relative cost-utility. Sampling uncertainty will be represented by plots on the cost-effectiveness plane and associated cost-effectiveness acceptability curves (CEACs). To reflect uncertainty and to enable valid inferences to be made, any missing data will be imputed using multiple imputation. This process will enable a decision about the acceptability of the intervention in terms of an effective use of NHS resources.

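### Baseline adjustment of SPADI and SF-36 depends on observed imbalance, and the AUC compared by t-test includes the pre-randomisation score

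*Protocol article*

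**What the plan says.** The Data analysis section fixes the following.

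- Primary comparison, SPADI at 12 weeks: "A two independent samples t-test will be used to compare mean SPADI total scores between the groups".
- Baseline adjustment by multiple regression or ANCOVA is to be used if the groups differ on baseline measurements. No threshold is given. The comparability check described just before names demographic and SF-36 data; it does not name SPADI.
- Secondary outcomes are to be handled in a similar way.
- For SPADI and SF-36 at baseline, 12, 24 and 52 weeks, a summary measure is calculated per patient, with the AUC given as an example. Then: "A two independent samples t-test will be used to compare mean AUC between the groups". That sentence names no baseline term.
- On the analysis population: "statistical analyses will be performed on an intention-to-treat basis". The section is silent on missing clinical data.

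The Economic analysis section carries the same intention-to-treat label, derives its QALYs from the SF-36 through the SF-6D, and adds that "any missing data will be imputed using multiple imputation".

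The Sample size calculation section states: "Assuming a standard deviation of 24 points, a power of 80% and a (two-sided) significance level of 5%, 91 participants per group will be required". It continues: "We will allow for a 15% loss to follow-up and aim to recruit 105 participants per group".

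**The concern.** Two choices are stated outright, so neither depends on what an unseen analysis plan may add.

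First, whether the primary estimate is adjusted depends on the baseline data. Without a threshold or a fixed list of covariates, two analysts could report different primary estimates from the same data. A baseline score earns its place in the model by its correlation with the outcome, not by chance imbalance between randomised groups. If the groups look balanced, the t-test keeps a standard error that still contains the baseline variation, and the precision available from a score already collected is lost.

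Second, treatment cannot affect a score taken before randomisation. Putting it in the AUC dilutes the treatment contrast and adds noise, unless baseline is also a covariate.

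At stake are the power of the primary comparison and the clarity of the one-year summary.

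**Working it through.** **Inputs.** From the Sample size calculation section: difference 10, SD 24, two-sided 5%, power 80%, 91 then 105 per group, 15% loss. From Data analysis: visits at 0, 12, 24 and 52 weeks. Assumed, because the protocol gives no figure: the same SD of 24 at every visit, an equal correlation ρ of 0.3, 0.5 or 0.7 between any two visits, and a constant 10-point effect after baseline.

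**The plan's own figure.** n = 2 × [24 × (1.960 + 0.842)/10]² = 90.4, so 91 per group, as stated. 91 × 1.15 = 104.65, so 105, as stated. (Dividing instead, 91/0.85 = 107.1, gives 108.) After 15% loss, 105 × 0.85 = 89 per group remain.

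**12-week power with 89 per group.** Power = Φ(10/SE − 1.96), with SE = SD × √(2/89).

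- Unadjusted: SE = 24 × 0.1499 = 3.60; Φ(2.78 − 1.96) = 79%.
- Adjusted for baseline, the SD becomes 24 × √(1 − ρ²):

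| ρ | residual SD | SE | power |
|---|---|---|---|
| 0.3 | 22.9 | 3.43 | 83% |
| 0.5 | 20.8 | 3.12 | 89% |
| 0.7 | 17.1 | 2.57 | 97% |

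**AUC weights** (trapezium rule, divided by 52 weeks):

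- baseline: 6/52 = 11.5%
- week 12: 12/52 = 23.1%
- week 24: 20/52 = 38.5%
- week 52: 14/52 = 26.9%

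A constant 10-point effect after baseline gives 10 × 46/52 = 8.85.

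**AUC power with 89 per group, effect 8.85.** The variance of the baseline-inclusive AUC is 24² × [ρ + (1 − ρ) × 776/2704], where 776 = 6² + 12² + 20² + 14². At ρ = 0.5 the SD is 19.3. Adjusted for baseline, the residual SD at ρ = 0.5 is 13.8.

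| ρ | baseline in AUC, t-test | baseline left out, t-test | baseline as covariate |
|---|---|---|---|
| 0.3 | 94% | 96% | 98% |
| 0.5 | 87% | 92% | 99% |
| 0.7 | 79% | 87% | >99% |

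The first step across each row is the cost of including baseline in the AUC; the second is the cost of not adjusting. Once baseline is a covariate, having it in the AUC as well does not change the treatment estimate or its standard error.

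**Effect of a chance imbalance.** One standard error of baseline SPADI is 24 × √(2/89) = 3.60 points. At ρ = 0.5 and no treatment effect, the AUC difference moves by 3.60 × (0.115 + 0.885 × 0.5) = 2.0 points. Of this, 3.60 × 0.115 = 0.4 comes from including baseline. The other 1.6 comes through the correlation of the follow-up scores with baseline and would be there with baseline left out.

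**The case against.** The case for leaving the plan alone is substantial.

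The protocol does provide for adjustment, and its statement that secondary outcomes follow a similar approach can be read as extending that to the AUC. The AUC is an example and belongs to secondary analyses. The primary t-test matches the basis of the sample size, and loss at the planned rate leaves 79% power. A chance imbalance is already reflected in the t-test's standard error, so it costs precision and does not bias the result. All of this stands. It limits the size of the point but does not answer it: adjustment is still conditional, without a threshold, and the AUC sentence names only a t-test.

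A reader might infer more about missing data than the text supports.

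- **That the clinical analyses are complete-case.** The article does not say so. It is silent on missing clinical data, which an article commonly leaves to the full protocol or analysis plan. Stating imputation for the economic analysis and nothing for the clinical one is not a contradiction.
- **That the AUC needs every questionnaire.** No such rule is given. A missed week 12 or 24 could be bridged by interpolation, which the Economic analysis section already uses for QALYs; a missed week 52 could not.
- **That only 61% would have a complete AUC.** That needs a fresh, independent 15% loss at each of three visits (0.85³ = 0.614, about 64 of 105 per group). The protocol gives a single allowance. If the same people are lost throughout, 85% (89 per group) remain.
- **That the t-tests are valid only if non-response is completely at random.** This is too strong. If non-response depends on baseline equally in both groups and the effect is additive, the difference in means is still unbiased.
- **That the analysis is not intention-to-treat.** The protocol does not define the term, and analysing available data by allocated group is a common use of it.

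**Conclusion.** The point holds as a matter of efficiency and prespecification. The protocol makes adjustment for baseline depend on what is observed, and it compares by t-test a summary in which 11.5% of the weight is the pre-randomisation score.

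Against 79% unadjusted, a prespecified baseline covariate would raise 12-week power by about 4, 10 or 18 percentage points at correlations of 0.3, 0.5 or 0.7. For the AUC the gain is about 5, 12 or 20 points. These sizes rest on the assumed correlations, a common SD of 24 and a constant effect. The direction is the same at each correlation examined.

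The planned t-tests are valid under randomisation, and the sample size reproduces. It is not established that the trial would be biased, underpowered at its planned rate of loss, or analysed on complete cases only.

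**What to change.** Prespecify adjustment for the baseline score of the same outcome, whatever the observed imbalance, and drop the conditional clause.

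Preferably, analyse SPADI and SF-36 each in one repeated-measures model at 12, 24 and 52 weeks, with baseline score, treatment, visit and treatment-by-visit. The model uses everyone with any follow-up. Keep the 12-week SPADI contrast as primary. In place of the AUC t-test, report a time-weighted post-baseline average from the same model, with its weights fixed in advance (for example the trapezium rule over weeks 12 to 52: 6/40, 20/40 and 14/40). A constant 10-point effect then appears as 10.

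The multiple imputation already planned for the economic analysis, which uses the same SF-36 returns, can serve as a sensitivity analysis for the clinical outcomes.

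The cost is a change of wording and slightly more analysis work, with no new data. The model assumes that data are missing at random. Standard multiple imputation shares that assumption, so it tests departures from it only if the imputed values are also shifted. If the simpler tests are preferred, a 12-week ANCOVA and a baseline-adjusted comparison of the summary measure would secure most of the gain.
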